**Data source and Sample Size**

RCGP-RSC data will be used for this study. These are from a database of coded primary care data from 135 UK General Practitioner (GP) practices – total population of approximately 1,250,000 patients. A large sample size is necessary for this study due to the variability in serum phosphate concentrations and the duration of the observational period (up to ten years).

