**Study Design**

This will be a retrospective study of the RCGP-RSC cohort. The data available were collected between April 2005 and March 2015 ([name] to confirm). These will be analysed using Read v2 (5-bit) codes to identify patients by the inclusion and exclusion criteria. Laboratory sample data will be taken from the laboratory sample results collected by GP practices.

Inclusion: One or more serum phosphate measurements recorded before a cardiovascular event (primary myocardial infarction; acute coronary syndrome; revascularisation procedure; ischaemic stroke; peripheral vascular disease; vascular dementia), or recorded in patients without any cardiovascular event in the study period. Patients will be aged 18 years and older.

Exclusion: Patients who have already had primary myocardial infarction; acute coronary syndrome or a revascularisation procedure before any serum phosphate measurements have been recorded. Patients with pre-existing ischaemic stroke, peripheral vascular disease or vascular dementia will also be excluded.

Serum phosphate will be a linear variable or analysed further as a categorical variable by range. ‘Time zero’ will refer to the first available serum phosphate measurement of a patient. The time to any outcome measure will be recorded and associations between serum phosphate and outcomes will be analysed by cox-regression.

In patients where more than one serum phosphate measure is available, the mean average of up to the first five measurements from time zero and before any cardiovascular event will be recorded and used in this study.

Importantly, confounding factors for cardiovascular outcomes in all included patients will form part of this study. For each variable, the selected single measurement will be chosen before the outcome measure and as close to time zero as possible, subject to data availability. The exceptions are baseline eGFR and albumin:creatinine ratio – the mean of two measurements in each case will be taken.

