**Statistical analysis**

Numerical data will be refined by excluding values beyond physiological limits. Data will be analysed using the statistical package R, with P values <0.05 being regarded as statistically significant. Expert statistical advice will be sought with the aim of using cox regression models to determine the association between serum phosphate and cardiovascular events, adjusting for the known cardiovascular risk factors. Cox proportional hazards multivariate models will also be constructed to provide a time-event analysis. A backwards stepwise elimination of variables approach will help to refine the model and evaluate the contribution of each variable towards the outcome measures.

Ethical considerations

Approval has been sought from the RCGP for the RSC database to be used for such research projects. Our study is retrospective and observational over anonymised patient data. The study involves no clinical interventions, no patient contact and no breach of confidentiality. The results of the study will be submitted for publication to a peer-reviewed journal.

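### The stated Cox models make no provision for the 135 practices in which patients are nested, so intervals can be too narrow and practice-level phosphate differences can bias the hazard ratio

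*Protocol*

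**What the plan says.** Under Data source and Sample Size, the data are described as "a database of coded primary care data from 135 UK General Practitioner (GP) practices", with a "total population of approximately 1,250,000 patients". Under Study Design, "Laboratory sample data will be taken from the laboratory sample results collected by GP practices". The exposure is built from these raw values: "the mean average of up to the first five measurements from time zero and before any cardiovascular event will be recorded". No standardisation across laboratories is described, and the protocol does not say how many laboratories are involved.

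The Statistical analysis section states the model in outline: "Expert statistical advice will be sought with the aim of using cox regression models to determine the association between serum phosphate and cardiovascular events", adjusted for known cardiovascular risk factors. It adds that "A backwards stepwise elimination of variables approach will help to refine the model" and sets the threshold, "with P values <0.05 being regarded as statistically significant".

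The candidate variables are listed under Confounding variables considered and Biochemical variables required. Intended output gives a results table with 20 rows. Practice and laboratory appear in none of these places, and Limitations does not mention clustering.

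**The concern.** Patients of one practice share test-ordering habits, event coding, local risk and possibly a laboratory. A one-level Cox model raises two separate problems.

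- **Precision.** If both phosphate and the outcome are correlated within practices, the usual model-based standard error is too small. The practices are large, so even small correlations may matter.
- **What the hazard ratio measures.** Without a practice stratum, the phosphate effect mixes differences between patients of one practice with differences between practices. If a practice's typical recorded phosphate is related to its risk or its coding, part of that relation is read as a phosphate effect. The protocol relies on a large sample to deal with phosphate variability. More patients reduce patient-level noise, but they do not remove differences shared by a whole practice.

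The phosphate hazard ratio, its interval and its p-value are the answer to the research question, so both problems bear on the main result.

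**Working it through.** The protocol gives no target sample size, power, event rate or intra-practice correlation (ICC), so there is no stated figure to reproduce.

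**Inputs from the protocol.** 135 practices; about 1,250,000 patients; significance at 0.05, taken as two-sided because the protocol does not say.

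**Assumed inputs.** 5% to 20% of patients have an eligible phosphate value; ICC of phosphate 0.02 to 0.10; ICC of the outcome 0.002 to 0.02.

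**Cluster size.** 1,250,000 / 135 = 9,259 registered patients per practice. At 5%, 10% and 20% tested, m = 463, 926 and 1,852.

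**Precision.** The approximate design effect for a patient-level covariate is DEFF = 1 + (m − 1) × ICC(phosphate) × ICC(outcome). The true standard error is √DEFF times the reported one. The actual error of a nominal 5% test is 2 × (1 − Φ(1.96/√DEFF)). For the middle case: 1 + 925 × 0.05 × 0.01 = 1.46; √1.46 = 1.21; 2 × (1 − Φ(1.62)) = 0.105.

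| m | ICC phosphate | ICC outcome | DEFF | SE ratio | Actual error |
|---|---|---|---|---|---|
| 463 | 0.02 | 0.002 | 1.02 | 1.01 | 0.052 |
| 926 | 0.05 | 0.002 | 1.09 | 1.05 | 0.061 |
| 926 | 0.05 | 0.01 | 1.46 | 1.21 | 0.105 |
| 926 | 0.10 | 0.01 | 1.93 | 1.39 | 0.158 |
| 1,852 | 0.10 | 0.02 | 4.70 | 2.17 | 0.366 |

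A wider grid (2% to 30% tested, phosphate ICC 0.01 to 0.20, outcome ICC 0.001 to 0.02) gives SE ratios from 1.001 to 3.48.

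**Bias.** A small null simulation used 135 practices of 100 patients and 60 replicates. It assumed a within-practice phosphate SD of 0.17, a practice-level phosphate shift with SD 0.05 and a practice log-hazard SD of 0.2.

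- Shifts unrelated to practice risk: the plain Cox model was unbiased, with a mean log HR of 0.0005 per SD of phosphate.
- Shifts correlated 0.5 with practice risk: the plain model gave a spurious log HR of 0.028 per SD (Monte Carlo SE 0.032/√60 = 0.004). Stratifying by practice reduced it to 0.002.

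The model SE in the simulation was 0.031. With 926 patients per practice and the same event rate it would be about 0.031/√9.26 = 0.010. A bias of 0.028 is then about 2.7 reported standard errors, so a small bias could produce a significant result in a cohort of this size.

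**The case against.** The strongest objection is that the point rests on silence. The protocol nowhere says that patients are independent. It says that statistical advice is still to come, and variance estimation is commonly left to an analysis plan, which was not available here. A reader might infer that the protocol has chosen to ignore clustering; the text does not support that. What remains is that the protocol already fixes the model type, the candidate covariates, the elimination method, the threshold and the results table, and none of these provides for practice. Whether phosphate is compared within or across practices also affects what the hazard ratio means, so it is more than a variance detail.

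A reader might also infer that laboratory differences are known to distort the phosphate effect. The protocol documents no such differences. Practices may share laboratories, and shifts unrelated to practice risk gave no bias in the null simulation. If phosphate has a true effect, such shifts would attenuate it.

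The covariates are not purely patient-level: the postcode-derived deprivation score is an area measure and may absorb some between-practice risk. It would not remove an assay offset.

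The middle case may be too pessimistic. Using ICC(outcome) ≈ p × s²/(1 − p), with p the share of patients with events and s the practice log-hazard SD, an ICC of 0.01 needs s of about 0.44 at p = 5% or 0.30 at p = 10%. With s = 0.2 and p = 5%, the ICC is 0.05 × 0.04/0.95 = 0.002, which is the second row of the table. This objection stands.

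With uncorrelated shifts the simulation showed no understated standard error (empirical SD 0.030, mean model SE 0.031). That is weak reassurance. At 100 patients per practice little inflation is expected, and an SD from 60 replicates has a Monte Carlo error of about 1/√(2 × 59) = 9%.

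Finally, stratification is not the only remedy, since a shared frailty is an alternative. Nor does stratifying by practice guarantee a comparison within one laboratory, because a practice's laboratory or assay may change over ten years.

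**Conclusion.** The point holds as a worthwhile and inexpensive improvement to the stated one-level model. It is not a contradiction or a demonstrated error in the protocol. Fitted as written, the models can give intervals that are too narrow. They can also give a biased hazard ratio if practice-level phosphate differences go with practice-level risk or coding.

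The size is unknown. The SE ratio runs from about 1.0 (negligible) to about 2.2 over the main assumed range, with 1.05 and 1.21 both plausible. The tested fraction and both ICCs are assumptions. The bias figure also depends on an assumed correlation of 0.5 between phosphate shifts and practice risk. It would be wrong to conclude that the intervals are certainly too narrow or that the hazard ratio is certainly biased.

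**What to change.** Add to Statistical analysis: all Cox models will stratify the baseline hazard by practice, and all confidence intervals and p-values will use a practice-clustered robust variance. The unstratified model will be reported as a sensitivity analysis.

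First confirm that the extract carries a pseudonymised practice identifier. The protocol describes the data as anonymised and does not mention one. Without an identifier the change cannot be made, and clustering should then be added to Limitations.

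With an identifier, the change takes about one sentence and standard model options in R. The price is slightly wider intervals and a small loss of between-practice information. Statistical advice is still to be sought, so the choice can be settled before any result is seen.

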**Primary Outcome Measure**

Composite cardiac (atherosclerosis) cardiovascular disease outcome measure of primary myocardial infarction; acute coronary syndrome; revascularisation procedure.

**Secondary Outcome Measure**

Individual cardiac (atherosclerosis) cardiovascular disease outcome measures: primary myocardial infarction; acute coronary syndrome; revascularisation procedure studied separately.

**Tertiary Outcome Measure**

Individual non-cardiac cardiovascular outcome measures: ischaemic stroke; peripheral vascular disease; vascular dementia.

**Study Design**

This will be a retrospective study of the RCGP-RSC cohort. The data available were collected between April 2005 and March 2015 ([name] to confirm). These will be analysed using Read v2 (5-bit) codes to identify patients by the inclusion and exclusion criteria. Laboratory sample data will be taken from the laboratory sample results collected by GP practices.

Inclusion: One or more serum phosphate measurements recorded before a cardiovascular event (primary myocardial infarction; acute coronary syndrome; revascularisation procedure; ischaemic stroke; peripheral vascular disease; vascular dementia), or recorded in patients without any cardiovascular event in the study period. Patients will be aged 18 years and older.

Exclusion: Patients who have already had primary myocardial infarction; acute coronary syndrome or a revascularisation procedure before any serum phosphate measurements have been recorded. Patients with pre-existing ischaemic stroke, peripheral vascular disease or vascular dementia will also be excluded.

Serum phosphate will be a linear variable or analysed further as a categorical variable by range. ‘Time zero’ will refer to the first available serum phosphate measurement of a patient. The time to any outcome measure will be recorded and associations between serum phosphate and outcomes will be analysed by cox-regression.

In patients where more than one serum phosphate measure is available, the mean average of up to the first five measurements from time zero and before any cardiovascular event will be recorded and used in this study.

Importantly, confounding factors for cardiovascular outcomes in all included patients will form part of this study. For each variable, the selected single measurement will be chosen before the outcome measure and as close to time zero as possible, subject to data availability. The exceptions are baseline eGFR and albumin:creatinine ratio – the mean of two measurements in each case will be taken.

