**Components**

Subjects: Retrospective cohort with serum phosphate recorded between 2005-2015

Setting: Primary Care dataset: RCGP-RSC cohort

Intervention: Serum phosphate measurements during the observation period

Outcome measure 1: Composite cardiac (atherosclerosis) cardiovascular disease outcome measure of primary myocardial infarction; acute coronary syndrome; revascularisation procedure.

Outcome measure 2: Individual cardiac (atherosclerosis) cardiovascular disease outcome measures: primary myocardial infarction; acute coronary syndrome; revascularisation procedure.

Outcome measure 3: Broader individual non-cardiac (atherosclerosis) cardiovascular disease outcome measures: ischaemic stroke; peripheral vascular disease; vascular dementia.

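### Time zero has no minimum look-back, so absence of earlier cardiovascular disease may rest on little or no prior record

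*Protocol*

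**What the plan says.** Study Design describes one body of data, with dates still marked for confirmation: "The data available were collected between April 2005 and March 2015". It goes on: "These will be analysed using Read v2 (5-bit) codes to identify patients by the inclusion and exclusion criteria". Components places the exposure in the same years: "Retrospective cohort with serum phosphate recorded between 2005-2015". Time zero "will refer to the first available serum phosphate measurement of a patient". Data source and Sample Size refers to "the duration of the observational period (up to ten years").

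Two exclusions deal with earlier disease. The cardiac one removes "Patients who have already had primary myocardial infarction; acute coronary syndrome or a revascularisation procedure before any serum phosphate measurements have been recorded". The other reads "Patients with pre-existing ischaemic stroke, peripheral vascular disease or vascular dementia will also be excluded". Neither gives a length of record to be searched. The protocol sets no registration time before time zero, does not say whether codes dated before April 2005 will be used, and gives no rule to separate an old event recorded late from a new one. Limitations mentions selection through blood testing and confounding, but not look-back.

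**The concern.** The Research question is about new events, and the primary composite includes primary myocardial infarction. An event can be called new only if an earlier one could have been seen. Here exposure, outcome and eligibility draw on the same ten years, and the clock may start on the first day of that window or on the day a patient joins a practice. For such patients, having no recorded history may only mean having no record.

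Two groups are exposed: patients whose first phosphate falls early in the window, and patients tested soon after registering. If some of them have existing disease, they enter as event-free and their next cardiovascular code counts towards the endpoint. The result would then partly describe recurrence in people with established disease. The Background section itself treats people with coronary artery disease separately from the general population.

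**Working it through.** The plan gives no figure for look-back, so there is none to reproduce. The check is date arithmetic followed by a comparison of two readings.

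**Inputs**
- Data window: April 2005 to March 2015, which is 10 years (Study Design).
- Longest follow-up: 10 years (Data source and Sample Size).
- Time zero: first phosphate on record, with no earliest date and no prior registration (Study Design).
- Phosphate window: 2005 to 2015 (Components).

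**Guaranteed look-back within the window**

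Look-back = length of window - longest follow-up = 10 - 10 = 0 years.

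**Look-back for a given patient**

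Let time zero fall *t* years after April 2005. The look-back within the window is at most *t*, so it ranges from 0 to 10 years. It is shorter for a patient who registered after April 2005, and it is 0 for one tested on registration.

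**Two readings of the data window**

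| | Extract holds only events dated from April 2005 | Extract also holds earlier-dated history |
| --- | --- | --- |
| Early time zero, long registered | Earlier events not visible | Earlier coded events visible, patient excluded |
| Tested at or soon after registration | Little or no look-back | Depends on what history is coded by time zero |
| Guaranteed minimum look-back | None | None |

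The second reading removes much of the problem for long-registered patients. Under neither reading does the protocol guarantee a recently registered patient any minimum record before time zero.

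**Size**

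The number misclassified depends on the prevalence of undetected disease, the event rates and the distribution of time zero. The protocol gives none of these, so the number cannot be computed.

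**The case against.** The strongest case against is that the exclusions carry no lower date limit. In their plain sense they cover any history before the first phosphate, and the sentence on the data window says when data were collected, not that older history is dropped. This stands. A reader might infer that a patient with an infarction before 2005 is certain to be kept, but the documents do not support that. Loss of earlier codes is possible, not stated.

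A reader might also fault the inclusion clause "or recorded in patients without any cardiovascular event in the study period" for testing absence of disease only within the window. That reading fails. The clause is the branch that admits patients who stay event-free during follow-up, and prior history is left to the exclusions.

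It is also true that the protocol does not describe how or when old notes are coded for new registrants. Late entry of history is therefore an assumption, and only the absence of a rule for it is a fact of the text.

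Finally, a minimum registration period might be placed in an SAP or extraction specification that is not shown. This does not dispose of the point. Eligibility, time zero and the data window are all set in the protocol, and the time-zero rule, followed as written, takes the first phosphate however short the preceding record.

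**Conclusion.** The point holds as a weakness in a stated rule: time zero can precede any usable look-back, so some prevalent disease may be counted as new. It should be corrected before extraction. It is not a contradiction in the protocol, and it does not show that the analysis would be invalid.

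The only firm figure is the guaranteed look-back of 0 years within the window. A reader might want to attach a contamination rate. With an assumed undetected prevalence *p* and event-rate ratio *r*, the share of events from such patients is *pr*/(*pr* + 1 - *p*):
- *p* = 0.02, *r* = 3: 0.06/1.04 = 5.8%
- *p* = 0.03, *r* = 5: 0.15/1.12 = 13.4%
- *p* = 0.05, *r* = 5: 0.25/1.20 = 20.8%

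None of these inputs comes from the protocol, so the range is no estimate for this study. A share of events is also not a bias in the phosphate hazard ratio. That bias would require undetected disease to be related to phosphate after adjustment, which the documents do not show, and its direction is unknown. Any effect is smaller if codes dated before April 2005 are in the extract.

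**What to change.** 1. State whether codes with event dates before April 2005 are held. Apply both exclusions to any qualifying history code with an event date before time zero, including those earlier dates where held.
2. Define time zero as the first phosphate after a minimum registered look-back. One option is 12 months after the later of 1 April 2005 and practice registration, or 12 months after registration alone if earlier codes are available. The 12 months is a proposal; the protocol offers no basis for a particular length. Tie the exclusions to this new time zero, so that an event between an earlier phosphate and time zero also excludes the patient.
3. Add a sensitivity analysis that varies the look-back or drops events soon after time zero. This matters most if earlier codes are not held, because a 12-month look-back need not reveal an older event.
4. Leave the inclusion clause about patients without an event during the study period as it is.

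The cost is a change to the extraction query and one date filter. Some early or newly registered patients are lost, and up to a year of follow-up.

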**Background**

Phosphate has many biochemical roles within the body. High serum phosphate predicts cardiovascular events in patients with chronic kidney disease, whilst low serum phosphate may be associated with risk reduction [1]. An association between cardiovascular events and elevated serum phosphate has also been reported in those with coronary artery disease [2], and also among the general population [3, 4, 5]. However, the precise molecular roles of phosphate in conjunction with cardiovascular risk factors are uncertain [1], and phosphate is yet to become an established marker or risk factor for cardiac events. Importantly, as vitamin D and calcium homeostasis overlap with phosphate regulation, the association of these minerals (plus parathyroid hormone) with the three outcomes will be investigated jointly. There is literature evidence that excess calcium and phosphate or their dysregulation may promote calcification during atherosclerosis [7].

The scope of this study aims to evaluate relationships between serum phosphate and the outcome measures. These outcome measures include two groups of cardiovascular events and we intend to examine them separately as follows:

Cardiovascular events due to atherosclerosis

Cardiac events (Outcomes 1 & 2) Non-cardiac events (Outcome 3)

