**Research question**

Is serum phosphate an independent predictor of new atherosclerotic cardiovascular disease events in patients stratified by renal function?

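### Known stable coronary disease is neither excluded nor adjusted for, while any later revascularisation counts towards the primary composite

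*Protocol*

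**What the plan says.** The Research question asks whether serum phosphate is an "independent predictor of new atherosclerotic cardiovascular disease events". The primary outcome is a composite of "primary myocardial infarction; acute coronary syndrome; revascularisation procedure", and nothing limits the last component to urgent or unplanned procedures.

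Eligibility is set in Study Design. The first exclusion covers "Patients who have already had primary myocardial infarction; acute coronary syndrome or a revascularisation procedure before any serum phosphate measurements have been recorded". The second reads "Patients with pre-existing ischaemic stroke, peripheral vascular disease or vascular dementia will also be excluded". Inclusion needs a phosphate value recorded before one of the six listed events, "or recorded in patients without any cardiovascular event in the study period", and age 18 or over.

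Under Confounding variables considered, the cardiovascular disease entry lists the same six conditions. Stable angina, coronary heart disease in any other coded form, and TIA are not named as exclusions, covariates or rows of the table under Intended output.

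**The concern.** The exclusion list mirrors the outcome list. That removes people who have already had a counted event, but not people whose coronary disease is already diagnosed and has not yet produced one. Such patients can be expected to reach the primary outcome more often than the rest. One route is specific to them: revascularisation treats existing coronary disease, so a planned procedure for disease known at time zero enters the composite on the same footing as a first infarction in someone with no known disease.

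The plan has no variable that separates the two groups. If known coronary disease is also related to phosphate after adjustment for the listed covariates, part of the phosphate hazard ratio will reflect that disease. This bears directly on the claim of independent prediction, which is the purpose of the study.

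**Working it through.** The protocol gives no sample size calculation, event count or event rate, so there is no figure to reproduce. The check is mainly a comparison of the lists.

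**Step 1. Compare the lists.**

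| Condition at time zero | Excluded (Study Design) | Covariate (Confounding variables considered) | Row in Intended output |
| --- | --- | --- | --- |
| Primary MI, ACS, revascularisation | Yes | Yes | No |
| Ischaemic stroke, peripheral vascular disease, vascular dementia | Yes | Yes | No |
| Stable angina, other coded coronary heart disease | No | No | No |
| TIA | No | No | No |

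**Step 2. Ask what the cardiovascular covariate can do.** Its six items are the six exclusions. Among eligible patients it is essentially constant at time zero, so it cannot adjust for baseline cardiovascular disease of any kind.

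**Step 3. Follow one patient.** An adult has coded stable angina, a first phosphate measurement and none of the six events. No exclusion applies, and the patient enters at time zero. A planned revascularisation two years later (an invented interval) meets the definition of the primary composite. No variable in the model records the angina.

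**Step 4. Look for a remedy elsewhere in the protocol.**
- Limitations states a general aim to control for cardiovascular risk factors based on QRISK2, but no angina or coronary disease term appears among the listed variables.
- Secondary Outcome Measure analyses the three cardiac components separately. This shows how far an association depends on revascularisation. It does not adjust the infarction or ACS analyses for known coronary disease.
- Statistical analysis uses backward stepwise elimination, so a term added without protection could be dropped.

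**Step 5. Illustrate the scale.** Let p be the share of the cohort with known coronary disease and no listed prior event, and r its primary-event rate relative to the rest. The share of primary events from this group is

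p × r / (p × r + 1 − p).

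The documents give neither p nor r. Both are assumed here.

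| p | r | Calculation | Share of primary events |
| --- | --- | --- | --- |
| 1% | 3 | 0.03 / (0.03 + 0.99) | 2.9% |
| 1% | 10 | 0.10 / (0.10 + 0.99) | 9.2% |
| 2% | 5 | 0.10 / (0.10 + 0.98) | 9.3% |
| 5% | 3 | 0.15 / (0.15 + 0.95) | 13.6% |
| 5% | 10 | 0.50 / (0.50 + 0.95) | 34.5% |

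The range is about 3% to 34%. It describes how many events the group might supply. It does not estimate any shift in the phosphate hazard ratio, which would also need the residual association between known coronary disease and phosphate.

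**The case against.** The strongest defence is that this is a coherent first-event design. The protocol asks about new events and excludes anyone who has already had one of them. A first revascularisation is literally a new event, even in a patient with known angina. A reader might infer that the eligibility rule contradicts the Research question; it does not, and the point should not be put that way. What stands against the defence is narrower: a design can be consistent about events and still leave a strong predictor of those events uncontrolled.

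The separate component analyses answer part of the endpoint concern, and that should be acknowledged. They leave the confounding untouched.

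Three other stronger readings are not supported:

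- **Background as a definition of the population.** The sentence "An association between cardiovascular events and elevated serum phosphate has also been reported in those with coronary artery disease" might suggest that the protocol treats coronary patients as outside its scope. It summarises literature, goes on to mention the general population as well, and does not define who is eligible here.
- **TIA and the primary outcome.** A reader might place prior TIA in the same argument. The primary composite is cardiac, so for a patient with TIA alone the gap matters chiefly for ischaemic stroke, a tertiary outcome.
- **Event share as bias.** A share of up to about a third of events might be read as bias of that order. Bias needs an association between coronary disease and phosphate that survives adjustment for age, eGFR, albumin:creatinine ratio, lipids, HbA1c, systolic pressure and smoking. The protocol gives no information on it.

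Finally, no Read code list is shown. Some angina codes, unstable angina in particular, may be captured under ACS. That could shrink the gap, but the protocol says codes are applied to the stated criteria, and nothing indicates broader lists.

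**Conclusion.** The concern holds in limited form. As written, patients with coded stable angina or other coronary heart disease and none of the six listed events are eligible, are not adjusted for, and can contribute a planned revascularisation to the primary composite. Possible confounding by known coronary disease therefore remains in the phosphate hazard ratio, and first onset is mixed with treatment of known disease. The reading of the text is firm, because eligibility, the composite and the covariate list are all set in the protocol.

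The consequence is less certain. Neither the direction nor the size of any bias can be derived from the document, and the event shares of about 3% to 34% rest wholly on assumed prevalence and relative rate. It would go too far to say that the primary result is uninterpretable. The supportable statement is that a plausible confounder has been left out of a study of independent prediction and can be put in cheaply.

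**What to change.** 1. Under Confounding variables considered and in the Intended output table, add coded angina or coronary/ischaemic heart disease dated on or before time zero. State in Statistical analysis that this term stays in the model whatever the backward elimination does.
2. Repeat the primary analysis without these patients. Alternatively, exclude them from the primary analysis itself by adding the diagnosis to the exclusions in Study Design.
3. For ischaemic stroke only, handle prior TIA in the same way.
4. Replace the present cardiovascular co-morbidity entry or explain its purpose, since its six items are already exclusions.

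The work is a few more Read codes applied to records already in the data source, and one more analysis. The real cost is fewer events in the restricted analysis: negligible if the group is small, but up to about a third of primary events at the top of the assumed range. The protocol gives no event count against which to judge that loss. This favours the covariate with a restricted repeat analysis, and the number of such patients and their events should be tabulated before the choice is fixed, without looking at their association with phosphate.
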